### Service delivery outcomes

1)   Time from birth to arrival at the study centre (hours).

2)   Proportion of patients with clear plastic bowel coverage at the time of arrival to the study centre.

3)   Proportion of patients with intravenous fluids prior to arrival at the study centre.

4)   Time from arrival to primary intervention (hours).

5)   Number and position of MDT members present during the initial resuscitation, primary intervention and defect closure.

6)   Proportion of patients receiving PN at some point during their hospital stay.

All patient data will be collected prospectively using
REDCap Data Capture Software
^128^. Data collection forms will be printed for real-time data collection at the patient’s bedside. This can be uploaded later to REDCap. Patient data entered into REDCap will be anonymous and local study teams will maintain a spreadsheet to keep track of REDCap IDs alongside the patient identifiable information. A pilot study was undertaken to ensure the data collection form is usable, appropriately worded and contains all the relevant content prior to project launch.

### Implementation outcomes

***Acceptability, adoption, appropriateness and feasibility.*** These will be evaluated and addressed during the qualitative studies, Delphi process and in-country co-development meeting to optimise the interventional bundle prior to implementation. Definitions are documented in the introduction section above. In order to evaluate these outcomes post-intervention, MDT members and parents will be invited to undertake a validated 12-item survey on acceptability, appropriateness and feasibility during the 4
^th^ week of the in-country implementation phase and again at the end of the study (
Supplementary File 6)
^110,
129^.

***Fidelity.*** The proportion of management protocol components completed as intended will be assessed using a checklist at the time of preformed silo application and defect closure. The checklist will be completed by the person undertaking the intervention for every neonate included in the study. A second observer, who has been trained in the gastroschisis management protocol, will independently complete the checklist for 50% of the cases.

Fidelity of the implementation process will also be evaluated as follows:

1)   Number of centres where the study leads inputted into the study design and protocol either via video conference with the PI and/or via internet communications.

2)   Total number and position of the MDT members* engaged in the qualitative study and/ or Delphi process from each study site.

3)   Did an in-person co-development meeting take place at the start of the implementation phase at each study site (yes/no).

   If yes, were adaptations made to the interventional bundle accordingly (yes/no).

   If yes, how many of each of the MDT members
^4^ were present during the meeting.

1)   Total number and position of the MDT members completing the MDT training day.

2)   Proportion of referral hospitals
^5^ (as identified by the study leads at each centre) receiving implementation of the pre-hospital management protocol through in-person education and training.

In order to accurately evaluate fidelity of both the interventional bundle and implementation process it will be important to distinguish between non-compliance and purposive adaptations
^130,
131^. Stirman
*et al*. have produced a framework and coding system for adaptations of evidence-based interventions that will be used to accurately document any deviations from the original plan at each site throughout the duration of the study
^132^.

***Coverage.*** The proportion of eligible patients who actually receive the intervention will be determined through the data entered into REDCap on all patients presenting with gastroschisis. Neonates with simple gastroschisis included within the study will have all data points completed. Neonates with complex gastroschisis excluded from the study intervention will have baseline data collected on the following: patient demographics, pre-hospital care and outcomes.

***Cost.*** The average cost per patient with gastroschisis will be estimated at the study centres, pre- and post-intervention. The implementation costs will also be calculated. The number of disability-adjusted life years (DALYs) averted through implementation of the interventional bundle will be calculated. The previously utilised disability-weight of 0.2 will be used for surviving neonates with gastroschisis where 0 is no disability and 1 is death
^2^. The cost in US$ per DALY averted will be calculated.

***Sustainability.*** The current intervention and implementation strategy have been evaluated for potential sustainability using the NHS Quality Improvement Sustainability Model
^133^. It scored 69.5/100 (19.8/31.3 for process, 43.1/52.4 for staff and 6.6/16.5 for organisation). A score above 55 is deemed ‘reason for optimism’. This evaluation has highlighted the need to set up a monitoring process beyond the life of the study, involve organisation leaders throughout the study process, to align the project with the team and organisation’s other strategy aims for improvement and to ensure facilities and equipment utilised are sustainable long-term. A re-evaluation will be undertaken just prior to interventional implementation and again following completion of the study.

## Data analysis

### Clinical outcomes

***Pre-post study analysis.*** Primary and secondary clinical outcomes will be compared pre- and post-intervention using chi-squared analysis for categorical variables or Fisher’s exact test if either of the groups contains less than 10 patients. For normally distributed continuous variables an unpaired t-test will be used and for non-normally distributed continuous variables a Mann-Whitney
*U* test will be used. P<0.05 will be deemed significant. Cases presenting during the 1-month implementation phase will be deemed post-intervention since the PI will be in attendance at all cases alongside the local team to assist with implementation of the protocol and training will have commenced.

***Time series analysis.*** Time series analysis will be undertaken using Statistical Process Control to distinguish significant trends and shifts in mortality from background variation during the study period
^134^.

***Multivariate analysis.*** Multivariate logistic regression analysis will be used to identify factors affecting all-cause in-hospital mortality with adjustment for confounding factors. Potential confounders include gestational age, weight, presence of co-morbidities, and ASA score at the time of primary intervention.

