### Sample size

It is estimated that between 240 to 384 patients with gastroschisis will present to the seven study centres during the 2-year data collection period (
Table 4). An estimated 75% of the neonates with gastroschisis should fulfil the inclusion criteria within the context of the study sites, equating to between 180 and 288 patients in the study in total (67–109 pre-intervention and 113–179 post-intervention). A successful pre-hospital component of the study may result in more patients presenting with simple gastroschisis and hence more being eligible for study inclusion.

**Table 4. T4:** The estimated number of gastroschisis cases per month at each of the study centres.

Site	Estimated no. cases/month	Dates for pre- intervention data collection at each site (total no. months)	Minimum no. pre-intervention cases,	Maximum no. pre- intervention cases	Timeframe for intervention implementation at each site in 2019	Dates for post- intervention data collection at each site (total no. months) *	Minimum no. of post- intervention cases	Maximum no. of post- intervention cases
**Korle-Bu TH,** **Ghana**	1	Oct 2018–May 2019 (7 months)	7	7	May 13 ^th^ – June 7th	May 2019 – Oct 2020 (17 months)	17	17
**Tamale TH, Ghana**	1–2	Oct 2018–June 2019 (8 months)	8	16	June 10 ^th^ – July 5th	June 2019 – Oct 2020 (16 months)	16	32
**Komfo Anokye TH,** **Ghana**	1	Nov 2018–July 2019 (8 months)	8	8	July 8 ^th^ – Aug 2nd	July 2019 – Nov 2020 (16 months)	16	16
**University TH** **Lusaka Zambia**	2–4	Nov 2018–August 2019 (9 months)	18	36	August 12 ^th^ – Sept 6th	Aug 2019 – Nov 2020 (15 months)	30	60
**ADCH, Zambia**	1	Jan 2019–Sept 2019 (8 months)	8	8	September 16 ^th^ – Oct 11th	Sept 2019 – Jan 2021 (16 months)	16	16
**KCH, Malawi**	2–4	Dec 2018–Oct 2019 (10 months)	20	40	October 21 ^th^ – Nov 15th	Oct 2019 – Dec 2020 (14 months)	28	56
**MNH, Tanzania**	2–3	Jan 2019–Nov 2019 (10 months)	20	30	Nov 25 ^th^ – Dec 20 ^th^	Nov 2019 – Jan 2021 (14 months)	28	42
**TOTAL**	**10 – 16**	**60 months**	**89**	**145**	**8 months**	**108 months**	**151**	**239**
**No. of patients** **with simple** **gastroschisis**	**8–12**		**67**	**109**			**113**	**179**

*Each site will collect 24 months of data in total

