In this study a convenience sample has been used and hence a post-hoc power calculation has been undertaken. Utilising a two-sided Z-test it has been calculated that at 90% power and p=0.05, the study could detect a difference in mortality of 16% (95% mortality down to 79%) if the minimum number of patients were included and a difference of 12% (95% mortality down to 83%) with the maximum estimated number.

This indicates that the study is appropriately powered. Some centres within sub-Saharan Africa have achieved a mortality rate of 80% or less, suggesting it is an achievable target.

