## Data collection

### Clinical outcomes

***Primary outcome.***

1) All-cause, in-hospital mortality.

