### Study impact

The systematic review, qualitative study and Delphi process will all provide unique evidence towards optimising care for neonates with gastroschisis in low-resource settings. Each study will be submitted for publication. The interventional study will allow for that evidence to be tested in-practice across seven tertiary paediatric surgery centres in sub-Saharan Africa. The study design will enable detailed analysis of which components of the interventional bundle and implementation strategy were and were not effective. Including multiple sites in the study will determine the generalisability of the intervention and will permit a more detailed analysis of contextual factors affecting outcome.

If successful, funding will be sought to scale-up the intervention to other sites across sub-Saharan Africa and then LMICs globally using a stepped-wedge approach. This has the potential to save the lives of hundreds of neonates born with gastroschisis. Since the majority of neonates with gastroschisis typically go on to live a full and normal life, the number of DALYs averted is very high. Gastroschisis has been described as a ‘bellwether procedure’ for neonatal surgery in low-resource settings
^2^. Hence, potentially improving the care for neonates with gastroschisis could also improve outcomes for neonates with other congenital anomalies that require a similar package of neonatal surgical care. This could have a wider global health impact in light of the recent Global Burden of Disease Report findings that congenital anomalies have recently risen to become the fifth-leading cause of death in children under 5 years globally
^136^.

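### The planned pre-post test of mortality has no calendar-time term, so about one year of background change counts as bundle effect, and no planned analysis gives a time-adjusted estimate

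*Protocol article*

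**What the plan says.** The primary outcome is "All-cause, in-hospital mortality" (Data collection, Clinical outcomes). Under Data analysis, Pre-post study analysis, the article states: "Primary and secondary clinical outcomes will be compared pre- and post-intervention using chi-squared analysis for categorical variables", with Fisher's exact test for small groups and "P<0.05 will be deemed significant". Patients seen during the implementation month count as post-intervention. Neither site nor calendar time is mentioned in this comparison.

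Two other mortality analyses follow in the same section. Statistical Process Control is to separate trends and shifts from background variation. A multivariate logistic regression is to identify factors affecting mortality; the confounders it names are gestational age, weight, co-morbidities and ASA score. The section on service delivery and implementation outcomes adds a time-series look at mortality after implementation.

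Table 4 (Sample size), in its column headed "Timeframe for intervention implementation at each site in 2019", gives seven staggered starts, from 13 May 2019 at Korle-Bu to 25 November 2019 at Muhimbili. Every site collects 24 months of data: 7 to 10 before and 14 to 17 after.

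The power statement under Sample size also compares two totals summed over sites, by a two-sided Z-test with 90% power and a 0.05 level. For the smaller total, the detectable effect is given as "a difference in mortality of 16% (95% mortality down to 79%) if the minimum number of patients were included". For the larger total it is 12 points, from 95% to 83%. Under Study impact the article says that "Including multiple sites in the study will determine the generalisability of the intervention".

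**The concern.** The study has no concurrent control group, so the pre-post comparison carries the effectiveness claim. At every site the post period is later than the pre period. If mortality was already falling for other reasons, such as better neonatal care, earlier referral or a change in practice ahead of the bundle, an unadjusted comparison credits that fall to the bundle.

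The article foresees some movement of this kind: Study limitations notes that teams involved in developing the bundle may change practice before implementation. It treats this only as something that could hide an effect, and does not list secular trend as something that could create one. A positive result is meant to support scale-up to other sites, so the credibility of the attribution matters.

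**Working it through.** **1. The plan's own power figure.** For a two-sided Z-test, power = Φ[(δ − 1.96·s0)/s1], where s0 is the standard error with pooled variance and s1 the standard error under the alternative.
- Minimum, 180 patients split equally (90 per group), 95% vs 79%: s0 = 0.0501, s1 = 0.0487, so (0.16 − 0.0983)/0.0487 = 1.27 and power is 89.8%.
- Maximum, 288 patients split equally (144 per group), 95% vs 83%: s0 = 0.0369, s1 = 0.0362, so (0.12 − 0.0723)/0.0362 = 1.32 and power is 90.6%.
- With the unequal groups that Table 4 implies (67 vs 113; 109 vs 179) the same formula gives 86.7% and 88.1%. Exact power of the uncorrected chi-squared test is 89.1% and 89.6%.

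The stated 90% therefore reproduces, for a comparison of two totals without a site or time term.

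**2. Time between the windows.** If a site has a pre months followed by 24 − a post months, the pre midpoint is a/2 and the post midpoint is a + (24 − a)/2 = 12 + a/2. The gap is 12 months whatever a is. Pooled over sites with Table 4 case rates, it is 11.8 months. A linear background fall of x points per year therefore adds about x points to the pre-post difference.

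**3. Effect on the planned test.** Inputs: pre mortality 95% (the power statement's baseline), post mortality 95% minus the assumed fall, no bundle effect, uncorrected chi-squared at two-sided 0.05, exact binomial enumeration.

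| Assumed fall per year | 67 vs 113 | 109 vs 179 |
|---|---|---|
| 0 points | 4.4% | 4.9% |
| 1 point | 4.9% | 5.7% |
| 2 points | 7.0% | 9.2% |
| 3 points | 10.4% | 14.9% |
| 5 points | 20.6% | 32.0% |

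**4. Site mix.** From Table 4 (minimum counts), Korle-Bu supplies 7/89 = 7.9% of pre cases and 17/151 = 11.3% of post cases; KCH supplies 20/89 = 22.5% and 28/151 = 18.5%. Half the sum of absolute differences in site shares is 8.2% (7.3% with maximum counts). If site mortality spans 10 points, the pooled difference moves by at most 0.082 × 10, or about 0.8 points.

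**5. Does site stratification help with drift?** No, because the 12-month gap lies within every site. In simulation with a 5-point yearly fall and no bundle effect, a site-stratified Mantel-Haenszel test still rejects in about 20% (minimum accrual) to 31% (maximum), and the stratified difference is still about 5 points.

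**6. Site plus calendar time.** Assumptions: linear trend, site fixed effects, linear probability model with robust standard errors, even arrivals at Table 4 rates. With background falls of 0 to 10 points per year and no bundle effect, rejection is about 4-6% and the mean estimate is about zero. Adding time multiplies the variance of the period effect by about 3.3 (standard error × 1.8; × 1.9 in a second simulation, from 0.047 to 0.089). Without a trend, power for the stated differences is about 30% (16 points, minimum) and 33% (12 points, maximum).

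**The case against.** Five counter-arguments deserve weight.

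- **The chi-squared test is not the only mortality analysis.** Statistical Process Control is aimed at trends. A reader might infer that the plan ignores time altogether, and the text does not support that. What remains is narrower: no rule links the charts to the bundle effect, they yield no adjusted estimate, and 1 to 4 cases per site per month near 95% mortality make them a weak check.
- **The confounder list is open-ended.** It says that confounders include those named, and a condensed article need not give a full model. The absence of site and time from the list does not prove that they will be left out. Even so, only patient-level factors are named, and the regression's stated purpose is to find factors affecting mortality.
- **Assumed drift may be too large.** The Introduction's long-run figures are slower: Thailand from 25% to 8% over 1986-2009 is 17/23, or about 0.7 points per year; high-income countries from over 90% to under 4% in half a century is roughly 86/50, or 1.7 points per year. At those rates the planned test rejects in about 4.5-5.2% and 6.2-7.9% of trials. This stands as a limit on the likely size, although those settings differ from the study sites.
- **Unequal site splits might be read as a serious bias, with stratification as the cure.** The figures support neither: the site-mix bias is small and stratification leaves drift in place.
- **The adjusted model is imprecise.** At about 30% power it will often fail to confirm a real effect. That is a reason for making it supporting and not primary.

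**Conclusion.** The point holds for calendar time. The stated test counts about one year of background change as bundle effect, and no analysis described in the article is tied to an estimate net of that change. The inflation of false positives is slight for a fall of 1 point per year and substantial at 5, where 21-32% of trials would be significant without any bundle effect. This rests on a 95% baseline, a linear trend and drift values that are assumptions.

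A reader might conclude that a significant result would be spurious. The documents do not support that: they give no trend at the study sites, and the 12 to 16 point differences in the power statement exceed the drift examined here. The statement that the study is appropriately powered applies only to the unadjusted comparison.

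**What to change.** Keep a simple pre-post comparison as primary. Preferably stratify it by site (Mantel-Haenszel test and stratified risk difference with 95% CI); this costs about 2% in standard error (0.053 to 0.054 in simulation).

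Pre-specify one required supporting analysis: a regression of mortality on period with site fixed effects and calendar time, drawing on the staggered starts of 13 May to 25 November 2019. Report its estimate and 95% CI beside the primary result. Name secular trend under Study limitations, and attribute the change to the bundle only as far as the time-adjusted estimate supports it.

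No new data are needed, since site is known and the planned time series already needs dates. The cost is precision: a standard error about 1.8-1.9 times larger and about 30% power for the stated differences. Disagreement between the two estimates should therefore be read from their intervals, and not from whether each is significant. The power statement should say that it covers the unadjusted comparison only.

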### Service delivery and implementation outcomes

Regression analysis will be undertaken to evaluate the impact of the service delivery outcomes and implementation outcomes including the acceptability (AIM) score, appropriateness (IAM) score, feasibility (FIM) score and fidelity on all-cause in-hospital mortality.

In order to assess sustainability during the post-implementation phase, fidelity of the interventional bundle will be analysed using time series analysis. This will assess whether fidelity remains stable, increases or declines following implementation. Time-series analysis will also be used to assess all-cause in-hospital mortality during the post-implementation phase to determine if there is an upwards, stable or downwards trend following implementation.

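### At the plan's own detectable effects only about 27–36 neonates survive, too few to fit the service delivery and implementation factors jointly by maximum likelihood without inflated effects

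*Protocol article*

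**What the plan says.** Under Data analysis, Clinical outcomes, the Protocol article states that "Multivariate logistic regression analysis will be used to identify factors affecting all-cause in-hospital mortality with adjustment for confounding factors". It continues: "Potential confounders include gestational age, weight, presence of co-morbidities, and ASA score at the time of primary intervention". The Abstract puts clinical and implementation factors under the same logistic method, adjusted for confounders.

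Under Data analysis, Service delivery and implementation outcomes, a regression is planned for the service delivery outcomes and the implementation outcomes, "including the acceptability (AIM) score, appropriateness (IAM) score, feasibility (FIM) score and fidelity on all-cause in-hospital mortality". Data collection lists six service delivery outcomes. One of them, staff number and position at three moments of care, is more than one variable. AIM, IAM and FIM come from a survey of staff and parents that starts in the fourth week of implementation, so they have no pre-intervention values.

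Study impact says that the design will "enable detailed analysis of which components of the interventional bundle and implementation strategy were and were not effective".

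Sample size gives the numbers: "equating to between 180 and 288 patients in the study in total (67–109 pre-intervention and 113–179 post-intervention"). It states that "at 90% power and p=0.05, the study could detect a difference in mortality of 16% (95% mortality down to 79"%), and "a difference of 12% (95% mortality down to 83%) with the maximum estimated number". No count of survivors, limit on predictors or estimation method is given.

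**The concern.** A logistic model is limited by the rarer of its two outcomes. At these mortality rates that is survival, so the 180 to 288 patients overstate the information available. When there are few survivors per predictor, maximum likelihood pushes log-odds ratios away from zero. The primary test is not at stake. What is at stake is the explanatory claim about which parts of the bundle and implementation strategy worked, since Study impact looks ahead to scale-up if the study succeeds. Overstated factor effects could influence what is carried forward.

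**Working it through.** **Inputs.** From Sample size and its Table 4: 67 pre and 113 post (minimum), 109 pre and 179 post (maximum). Mortality is 95% before, and 79% (minimum) or 83% (maximum) after.

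**Reproducing the plan's power.** The arcsine form is power = Φ(h·√(n₁n₂/(n₁+n₂)) − 1.96), with h = 2·asin√0.95 − 2·asin√p₂.
- Minimum: h = 0.501 and √(67×113/180) = 6.49, giving 90.1%.
- Maximum: h = 0.399 and √(109×179/288) = 8.23, giving 90.7%.

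The stated 90% is therefore reproduced. The pooled-variance form gives 86.7% and 88.1%, and the unpooled form 92.9% for both.

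**Expected survivors** = n_pre × 0.05 + n_post × (1 − p₂).
- Minimum: 67×0.05 + 113×0.21 = 3.35 + 23.73 = 27.1.
- Maximum: 109×0.05 + 179×0.17 = 5.45 + 30.43 = 35.9.

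**Survivors per predictor.**

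| Model | Minimum | Maximum |
|---|---|---|
| Period + 4 named confounders (5 terms) | 27.1/5 = 5.4 | 35.9/5 = 7.2 |
| 10 service delivery and implementation factors, post only | 23.73/10 = 2.4 | 30.43/10 = 3.0 |
| The same 10 + 4 confounders, post only | 23.73/14 = 1.7 | 30.43/14 = 2.2 |

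Ten is a low count, because the staffing item expands to several variables.

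**Bias under maximum likelihood.** These results come from simulation. The covariate effects are assumptions: log-odds 0.5 per SD for continuous covariates and, where binary covariates were included, 0.7.
- Period + 4 confounders: mean inflation of covariate log-odds ratios 6% (minimum) and 4% (maximum).
- Post only, 10 factors: 18–24% at n=113 and 10–13% at n=179, depending on the assumptions.
- Post only, 14 predictors: 30–32% at n=113 and 20–21% at n=179. One n=113 setting, in which all 14 predictors had an effect, gave a mean of 38% (median 28%).

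For scale, take a true odds ratio of exp(0.5) = 1.65. It would be estimated on average near exp(0.55) = 1.73 with 10% inflation, or exp(0.65) = 1.92 with 30%.

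**Bias under Firth.** Mean bias was about 1% in the 5-term and 15-term pre-post settings, and 1% or less in post-only settings with 10 and 14 predictors (half with a true effect).

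**Failed fits.** The period term cannot be estimated by maximum likelihood if no pre-intervention neonate survives: 0.95^67 = 3.2% or 0.95^109 = 0.4%. In simulation, 0.3–4.4% of 5-term fits failed, and 0–0.5% of post-only fits.

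**Sensitivity to the assumed benefit.** Total survivors would be 15–23 at 90% post-intervention mortality, 26–41 at 80%, 37–59 at 70% and 60–95 at 50%. With 14 predictors and n=113, inflation was still 26% at 70% mortality and 24% at 50%.

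**The case against.** The strongest reply is that the document never commits to a crowded model. The logistic regression under Clinical outcomes names four confounders. The ten other measures belong to a separate section that does not say how many models there are or whether factors enter together. The estimation method is not stated either, Firth regression is itself logistic regression, and such detail is often left to an analysis plan. Much of this stands. The point is therefore conditional on joint entry and maximum likelihood, and it supports a cheap improvement rather than a charge of missing detail. What remains is that the article fixes the outcome, the logistic method and the list of factors, and promises conclusions about components that its own numbers support only weakly.

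A reader might infer five stronger claims that the documents do not support:
- **One 15-term pre-post model.** Four confounders, period and ten factors add up to 15, but no section puts them in one model. AIM, IAM and FIM do not exist before implementation, so they could not enter a pre-post model as ordinary patient covariates.
- **27–36 as a forecast.** These counts belong to the detectable differences. The plan says: "Some centres within sub-Saharan Africa have achieved a mortality rate of 80% or less, suggesting it is an achievable target". A larger benefit gives more survivors and a smaller one fewer.
- **Models will separate.** Failure is possible but uncommon. Even a hypothetical 15-term model failed in only 0.6–7.4% of simulated fits.
- **Site terms will separate.** Site is not a named term. A small site may well have no pre-intervention survivor, but a site main effect separates only if the site has none in either period. With 6 pre and 12 post cases the chance is 0.95^6 × 0.79^12 = 4.3%, or 7.9% at 83% mortality.
- **Spurious factors will be picked.** Rejection per null factor was about 6–7% against a nominal 5%. With 14 predictors, half of them null, at least one null factor reached significance in 32–34% of runs. Multiplicity alone gives 1 − 0.95^7 = 30%. This is a reason to state the number of comparisons, not evidence of sparse-data error.

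It is also fair to say that the bias is modest beside the imprecision. In a 15-term model at minimum n, the period coefficient averaged −1.96 against a true −1.65. That gap of 0.31 is less than half its standard error of about 0.7.

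**Conclusion.** The concern holds for the models meant to identify service delivery and implementation factors. At the plan's detectable effects they would have about 2 to 3 survivors per predictor if fitted jointly, and maximum likelihood would inflate log-odds ratios by roughly 10–30%. The survivor counts follow directly from the Sample size section. The inflation figures rest on assumed covariate effects and on joint entry, which the article neither states nor rules out.

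The adjusted pre-post model with the named confounders is in reasonable shape: 5.4 to 7.2 survivors per term, about 4–6% covariate inflation, and a 0.4–3.2% chance that the period effect cannot be estimated. The primary chi-squared comparison is unaffected. This is a worthwhile, inexpensive improvement to secondary analyses and does not threaten the main result.

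**What to change.** - Fit all mortality regressions by Firth penalised likelihood with profile-likelihood intervals. This also gives a finite period estimate if no pre-intervention neonate survives.
- Keep the adjusted pre-post model to period plus gestational age, weight, co-morbidities and ASA score.
- Add service delivery and implementation factors to that base one at a time. This leaves 27.1/6 = 4.5 to 35.9/6 = 6.0 survivors per term. For AIM, IAM and FIM use post-intervention patients only and drop period: 23.73/5 = 4.7 to 30.43/5 = 6.1.
- Report these factor analyses as exploratory and state the number of comparisons (at least ten). Say how survey scores are assigned to patients, since one average per site gives at most seven distinct values.
- Soften the Study impact statement: the design can explore associations between components and mortality, not establish which were effective.

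The cost is a change of analysis wording, with methods available in standard software. The downside is that fewer factors are adjusted for one another. Firth estimation removes most of the bias but adds no information, so intervals will remain wide.
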